## Oral immunotherapy for young children with peanut allergy – Small Children OIT (SmaChO)

### Materials and Methods

#### Study population

Children aged 12-47 months with IgE-ab to peanut extract and/or Ara h 2  $>0.1$  kUA/L are identified via the Karolinska University Laboratory in Stockholm. All eligible families will receive an information letter about the study. Interested families with children with possible peanut allergy (groups 1 and 2) will be able to contact the study team. If we do not receive enough potential participants, renewed contact is made by telephone to investigate if there is an interest in participating in the study. Children/families can also be recruited on the visits to allergy clinics or be referred to by colleagues from other healthcare facilities in Stockholm. Children without allergies will be asked to participate as a healthy control group (group 3).

Children, 12-47 months at inclusion, (n=75 with peanut allergy; at least one objective symptom at a peanut challenge and IgE-ab to peanut/Ara h 2  $>0.1$  kUA/l). Families who want their child to have peanut OIT will be randomized 2:1 to either group 1 or 2.

**Group 1;** 50 children, randomized to treatment: peanut OIT with slow up-dosing every 4-6 weeks (in total 40-60 weeks up-dosing period), until a maintenance dose of 285 mg peanut protein, total treatment time 3 years.

**Group 2;** 25 children, randomized to continue with peanut avoidance. This group will be offered OIT after the study is finished if there is a clinical available OIT to peanut at that time point.

**Group 3;** healthy controls: 20 children 12-47 months without allergic disease.

**Outcomes:** The primary outcome is defined as sustained unresponsiveness to 750 mg peanut protein (cumulative dose) at an open oral peanut challenge 4 weeks after 3 years of OIT was stopped (group 1 and 2). Secondary outcomes are adverse events among peanut allergic children with/without OIT treatment (group 1 and 2), and changes in quality-of-life parameters and immunological markers (group, 1, 2, 3).

#### Inclusion criteria

- Children 12-47 months at inclusion
- Positive baseline challenge at a maximum of the 250 mg peanut protein-dose and with at least one objective symptom at peanut challenge or positive peanut challenge performed in the clinic in a similar way within 1 year from study start
- IgE-ab to peanut and/or Ara h 2  $\geq 0.1$  kUA/l, analyzed within 12 months from start of study
- Written consent for participation in the study from all caregivers

#### Exclusion criteria

- Other serious illness
- Previously life-threatening anaphylaxis (intensive care), regardless of the triggering agent

- A history of eosinophilic esophagitis (EoE), other eosinophilic gastrointestinal disease, severe chronic gastroesophageal reflux disease (GERD), symptoms of dysphagia, unclear recurrent GI disorders
- Participation in another intervention study, if included in intervention group
- Severe uncontrolled asthma
- Ongoing medication with biological drugs or oral steroids

#### **Individual stopping criteria (i.e. the OIT is discontinued for that specific child):**

- Children who wishes to no longer participate in the intervention (but who may remain in the study for further observation)
- More than 2 anaphylactic reactions, strongly consider cessation of intervention

#### **Stopping criteria for the whole study (after discussion with members of security board):**

- More than 50% of the patients experience at least 2 OIT related anaphylactic reactions.
- Fatal reaction to peanuts among any of the participants in group 1 (the OIT-group)

#### **Randomization procedure**

STATA program version 15.1 is used to generate the random allocation sequence. To avoid unnecessary imbalance in the number of subjects allocated to each group, allocation is made by the program within blocks of reasonable size computed by the program. The pattern of the blocks is randomized by the program and concealed for the study group. The randomization protocol and the allocation sequence is saved into a user-named STATA data-file with information of commands and specified options. The list with the allocation sequence is given to an administrator outside the project who prepares numbered sealed opaque envelopes containing allocation group and study identification number. The envelope is opened together with the family after a positive peanut challenge and a signed consent.

#### **Power calculation**

The number of study participants is in the same order of magnitude as in previous similar studies and is also adapted to the logistical and economic conditions and the number of existing children in Stockholm that may be relevant for the study. A power calculation (80% power, 5% significance level) provides that if we want to demonstrate a difference in tolerance level of 10% in group 2 without treatment and 50% in group 1 with OIT peanut, 30 study participants are required in group 1 and 15 participants in group 2. If the success rate is 10% in group 2 and 75% in group 1 only 12 participants with active treatment and 6 controls are needed. Power calculation in STATA 15.1.

#### **Blood and fecal samples**

With the support of preliminary findings in our previous OIT peanut study, we want to analyze how the lymphocyte population is affected in young children during oral immunotherapy to

peanut. We intend to study the T cell population of these children *ex vivo* with and without stimulation and correlate to the intestinal microflora.

Blood samples (20 ml/time-point) will be collected at baseline, at year 1, 2 and 3, Table 1, for:

1. Immunoglobulins, e.g. IgE, IgG4 will be analyzed with ImmunoCap (ThermoFisher Scientific, Uppsala, Sweden).
2. Immunological markers on peripheral blood mononuclear cells will be analyzed *ex vivo* with flow cytometry, as well as with RNA sequencing platforms.
3. Circulating immune factors in plasma such as cytokines and chemokines will be measured in plasma by ELISA-based assays
4. Peripheral blood mononuclear cell populations will be exposed to different stimuli (e.g. peanut, anti-CD3/CD28 beads) *in vitro*, and the type and level of the response of the different mononuclear cell populations will be monitored at mRNA and protein levels.

Fecal samples will be collected at baseline, at year 1, 2 and 3, Table 1, for:

1. Investigations of the gut microbiome with sequencing-based methods to monitor possible changes in the gut microbiota composition and function related to the treatment

The blood and fecal samples will be stored at the Biobank at Södersjukhuset in accordance with current regulations. All data after analyzing will be entered into the database RedCap, which is stored at Karolinska Institutet, Södersjukhuset in accordance with applicable rules.

## Questionnaires

Information about Quality of life will be collected at base-line and at year 1, 2 and 3 (Table 1). Food Allergy Quality of Life Questionnaire-parental Form (FAQLQ-PF) will be used. All data will be entered into the database RedCap, which is stored at Karolinska Institutet, Södersjukhuset in accordance with applicable rules.

## Intervention substance

For the lower peanut OIT doses we will for practical reasons use peanut flour (peanøttmel, 50% protein content, Sukrin, Oslo, Norway) mixed with oat flour (Havremjöl glutenfritt, Urtekram, Midsona AB, Jylland, Denmark). For higher OIT doses (from 32 mg peanut protein) and the maintenance dose we will use “BAMBA” - a peanut-coated corn puff that dissolves in the mouth and contains 50% peanut and used in the LEAP study (Osem Food Industries, Shohan, Israel).

## Visits - groups 1 and 2

**Visit 1, screening visit, duration 1 hour:** the child and parents come to the Research Center at Sachs' Children and Youth Hospital for an information and screening visit. Written consent from both parents / legal guardians is mandatory to participate in the study. At the visit the families will be informed about the study design, follow-up schedule and adverse events that

may arise. A medical history on previous allergic reactions to peanuts and other background factors is collected. If necessary, the study physician will also review the medical records. Materials for fecal samples are provided.

**Visit 2, baseline challenge, duration 6 hours:** all children with a suspected peanut allergy, groups 1 and 2, undergo an open peanut challenge with peanut flour using (Table 2a). Before the start of the challenge, the child is examined by the physician according to a pre-set form. Only children free of infections and ongoing allergic symptoms may undergo challenge. For safety reasons, all children will receive a peripheral venous catheter after local anesthesia (EMLA). From the peripheral venous catheters, blood samples for immunoglobulins, blood status and immunological markers (20 ml) will be drawn (Table 1). Questions about quality of life will be answered by the parents. Observation time will be 2 hours after the last dose. If the child has undergone an equivalent challenge in the clinic within 1 year, no new challenge needs to be done.

A positive challenge is defined as at least one objective sign of allergic reaction (e.g. urticaria, flush, swelling/angioedema, nasal symptoms, eye symptoms, hoarseness, persistent cough, wheezing, stridor, abdominal pain (affecting the child's general condition), nausea, vomiting, diarrhea, hypotension, affected oxygenation) within 2 hours after the last dose. The challenge is interrupted immediately upon objective allergic symptoms and adequate drugs (such as antihistamine, intramuscular adrenaline, inhalation of beta-2-agonist and oral cortisone) are given to interrupt the reaction. The given dose when allergic reaction occurs will be noted and symptoms graded in a template.

After a positive peanut challenge with objective symptoms at maximum dose 4 (250 mg peanut protein) and signed parental consent, the child will be randomized 2:1 to either the OIT- (group 1) or control group (group 2).

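### The definition of a positive challenge calls for an objective sign but counts unqualified nausea as one, so a sensitised but tolerant child could be randomised on apparent nausea alone

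*Protocol*

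**What the plan says.** The Inclusion criteria ask for a positive baseline challenge "with at least one objective symptom at peanut challenge", or a similar positive clinic challenge within 1 year. The Visit 2 text (Visits - groups 1 and 2) supplies the definition: "A positive challenge is defined as at least one objective sign of allergic reaction". One sign is enough.

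Examples follow in brackets. Most can be seen or measured, such as urticaria, swelling, wheezing, vomiting and hypotension. One complaint is limited: "abdominal pain (affecting the child's general condition". Nausea is not: "nausea, vomiting, diarrhea, hypotension, affected oxygenation) within 2 hours after the last dose".

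The challenge is open: the children "undergo an open peanut challenge with peanut flour". The result decides entry: "After a positive peanut challenge with objective symptoms at maximum dose 4 (250 mg peanut protein) and signed parental consent, the child will be randomized". Besides the challenge, the allergy-specific criterion is IgE to peanut and/or Ara h 2 of at least 0.1 kUA/l, "analyzed within 12 months from start of study".

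The primary outcome is also judged "at an open oral peanut challenge 4 weeks after 3 years of OIT was stopped (group 1 and 2"). For the later challenges the protocol says:

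- **Group 2, years 1 and 3:** the baseline schedule (Table 2a) is repeated, with no separate rule for a positive result.
- **Group 1, Visit 23:** the result is judged by the absence of dose-limiting symptoms at 750 mg cumulative. The term is not defined.
- **Group 1, Visit 24:** the challenge is one that children pass, but no pass criterion is given.

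**The concern.** Nausea is something a child feels. An observer sees only what goes with it, such as retching, and vomiting already has its own place in the list. The separate entry therefore adds the cases where nothing has come up. Abdominal pain in the same list has a qualifier, so the need to limit a complaint was recognised there and not for nausea.

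This matters most at entry. The challenge is what separates allergic from merely sensitised children. Children of 12-47 months cannot report nausea reliably, so a parent or staff member who knows that peanut was given must largely infer it. A sensitised but tolerant child who looks nauseous then meets the written rule and is randomised. Such a child would be expected to pass later with or without OIT, which pulls the two arms together. An analysis plan cannot repair this after randomisation.

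**Working it through.** **1. The text.** The definition requires an objective sign, one sign is enough, nausea is listed, and nothing limits it to visible nausea. Read literally, nausea alone makes the challenge positive and opens the way to randomisation. The IgE criterion does not close the gap, because a sensitised child can be tolerant.

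**2. The plan's own figures (Power calculation).** Inputs: 10% vs 50% or 75%, 80% power, 5% significance, 2:1 allocation. With a two-sided test, the pooled-variance formula and no continuity correction, the required control-arm size is

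n = [1.96·√(p̄(1−p̄)(1+1/2)) + 0.84·√(p₁(1−p₁) + p₂(1−p₂)/2)]² / (p₂−p₁)², with p̄ = (p₁+2p₂)/3.

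This gives 15 and 30 for 50%, and 6 and 12 for 75%, exactly as stated. Those figures are not in dispute.

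**3. Dilution at entry.** Let f be the share of entrants who are tolerant and would pass in either arm. The protocol does not give f, so the values below are assumptions. They also suppose a year-3 challenge on which either arm could register a pass.

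Observed rate = f + (1−f)·planned rate. Power at 25 and 50 children is Φ[(d − 1.96·SE₀)/SE₁], where d is the difference, SE₀ the pooled and SE₁ the unpooled standard error.

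| f | Group 2 | Group 1 | Difference (points) | Power |
|---|---|---|---|---|
| 0 | 10% | 50% | 40 | 96.6% |
| 2% | 11.8% | 51.0% | 39.2 | 95.2% |
| 5% | 14.5% | 52.5% | 38 | 92.7% |
| 10% | 19% | 55% | 36 | 87.7% |
| 20% | 28% | 60% | 32 | about 76% |

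Worked for f = 10%: 0.10 + 0.90×0.10 = 0.19 and 0.10 + 0.90×0.50 = 0.55. SE₀ = 0.1213 and SE₁ = 0.1054, so (0.36 − 0.2377)/0.1054 = 1.16 and Φ(1.16) = 87.7%.

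**4. Year 3.** Using the Visit 2 definition here is an inference, since Group 2 is told only to repeat the schedule. Table 2a adds up to 0.3 + 2.5 + 25 + 250 = 277.8 mg, so a Group 2 child on that schedule cannot reach 750 mg whatever is done about nausea.

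Suppose, for illustration only, that Group 2 could reach 750 mg and that nausea wrongly failed 10% of its truly tolerant children and none in Group 1. A true 10% would be observed as 0.10×0.90 = 9.0%. With no treatment effect, the chance of a two-sided Fisher exact result at 5% in favour of OIT (25 vs 50) would rise from 0.94% to 1.23%. At 30% true tolerance in both arms it would rise from 1.86% to 3.35%. For reference, half of 5% is 2.5%.

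**The case against.** The strongest reply is that the governing words are *objective sign of allergic reaction*. The list is only of examples, symptoms are graded in a template that is not shown, and the randomisation sentence repeats that symptoms must be objective. In children this young, staff must largely score what they see, and nausea can be part of a true reaction. A careful physician may well count only manifest nausea. All this makes nausea-only entry less likely, but nothing in the text requires that reading, and the qualifier given to abdominal pain shows how easily one could have been added.

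Several further points stand and limit the finding:

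- Abdominal pain is already qualified and needs no change.
- The 100 g portion at dose 4 of Table 2a is not a sound argument for nausea from volume, because the table offers 1 g of peanut butter instead.
- The share f is assumed, and not every child admitted on nausea would be tolerant.
- At the planned size, power stays above 80% with f up to 10%.

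A reader might go further and infer that the nausea item biases the primary comparison towards OIT, because avoidance-arm children would feel nauseous from fear or aversion. The documents do not support that. They do not say that the Visit 2 definition governs year 3. Group 1 can fail on nausea too, so bias needs a difference between arms that nothing in the protocol establishes. Dilution at entry works in the opposite direction, and the Group 2 schedule stops short of 750 mg in any case.

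**Conclusion.** The point holds for entry. The protocol rests eligibility on an objective sign and then counts a subjective symptom as one, without qualifier, in an open challenge in very young children. The consequence is possible dilution of the treatment contrast: from 40 to 36 points if 10% of entrants were tolerant, and to 32 points if 20% were. Only the 20% case takes approximate power at 25 and 50 children below 80%. Both shares are assumptions, and the size cannot be determined from the document.

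The year-3 effect is secondary and its direction unknown. What can be said is that no other definition of a positive challenge is given, that Group 1 is judged at Visit 23 in a different and undefined term, and that Visit 24 has no criterion. The shortfall of the Group 2 schedule against 750 mg is a separate and larger problem. The definition is worth correcting because a key rule contradicts itself and the correction is small. It does not show that the planned comparison is invalid.

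**What to change.** For scoring eligibility and the primary outcome:

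1. Reconcile the list in the Visit 2 definition with the word *objective*: nausea alone, without an observable sign, is not counted as an objective sign. Leave abdominal pain with its existing qualifier.
2. Record nausea separately as a subjective symptom on the challenge form.
3. Apply one scoring definition to both arms at every challenge, and reconcile it with the wording for Group 1 Visits 23 and 24 and Group 2 Visits 3 and 4.
4. State in advance, identically for both arms, how a challenge ended for subjective symptoms alone is classified, so that every child challenged has a primary result. A separate inconclusive category would create missing primary outcomes and leave the path after challenge 3 undefined.
5. Add a sensitivity analysis that reclassifies those challenges in both arms.

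This concerns scoring only. The Visit 2 text ties the same signs to interruption, so the edit should say that when to interrupt a challenge and how to treat the child stay with the study physician.

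The cost is an edit to the definition and the challenge form, plus the reconciliation with the later visits. The downside is that a few children with nausea only would not qualify on that challenge.

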### **Group 1, Peanut Allergic Children Undergoing OIT Peanut, Slow Up-dosing**

#### **Visit 3, week 0, duration 6 hours: start immunotherapy:**

Clinical examination of the child is performed and noted in a standardized form. The peanut OIT starts with 1/4 of the dose (at least 3 mg of peanut protein) that gave the first reaction at baseline challenge, e.g. if reaction occurred at 100 mg of peanut (25 mg of peanut protein), the start dose will be 6 mg. Four doses will be given at the study center with 20-30 min intervals with 0.8, 1.5, 3 and 6 mg of peanut protein. The patient will be observed for 90 minutes after the last dose. If the last dose of peanut protein is tolerated (in the example 6 mg), this dose will be ingested daily at home for 4 weeks (Table 3) in the form of peanut flour mixed with oat flour for the lower doses and Bamba (a peanut-coated corn puff that dissolves in the mouth and contains about 50% peanut protein) from dose 32 mg peanut protein. The study participants are provided from the study center with peanuts in the appropriate form and quantity.

The families receive information on how to fill in a diary at home, which records daily intake of peanut, adverse events (all symptoms that occur during the study period regardless of whether they can be associated with peanut intake) and drugs that the child receives during the study period. The diary is filled in by the parents between the visits and taken to all visits where the study physician goes through the diary together with a parent/the parents.

All study participants will get an "emergency kit", adrenaline autoinjector for intramuscular injection, antihistamine, and b2-agonist for inhalation if the participant has a known asthma. Oral corticosteroids will be provided if the family lives far away from hospital; corticosteroids take 2-3 hours before effect. The parents receive written instruction and a practical demonstration on how/when to use the medications. They will also get instructions on when to contact the study team and/or make an acute hospital visit.

All study participants are instructed to strictly avoid any other intake of peanuts, apart from the OIT doses.

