**Table 2a. Protocol for baseline peanut challenge (and for Group 2 also after 1 and 3 years)**

| Dose | Amount of peanut mixture*       | Amount of peanut protein, mg |
|-------------|----------------------------------------|-------------------------------------|
| 1           | 0,1 g mixture                          | 0,3                                 |
| 2           | 1 g mixture                            | 2,5                                 |
| 3           | 10 g mixture                           | 25                                  |
| 4           | 100 g mixture
(or 1g peanut butter) | 250                                 |

\*Mixture: 0.2g peanut butter mixed with 19.8g of something the child can eat

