**Table 3a. Start of immunotherapy, mini up-dosing (for low doses)**

| Dose nr | Amount peanut protein, mg | Amount peanuts, mg | Amount peanut flour 10%* in mg (4,6% peanut protein) | Interval (min) |
|---------|---------------------------|--------------------|------------------------------------------------------|----------------|
| 1       | 0.8                       | 3.2                | 17                                                   | 30             |
| 2       | 1.5                       | 5.6                | 33                                                   | 30             |
| 3       | 3                         | 11                 | 65                                                   | 30             |
| 4       | 6                         | 22                 | 130                                                  | 30             |

\*Mix 1g Peanut powder with 9g oat flour

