**Table 3b. Schedule for slow up-dosing: Starting dose is calculated from reaction dose at the baseline challenge**

| Dos nr | Amount of peanut protein, mg | Amount of peanut flour 10%* in mg (4,6% peanut protein) | Amount of peanuts, mg (one peanut approx. 800 mg) | Pieces of Bamba (700mg/piece, protein content 17,5%) | Interval, weeks | % increase |
|--------|------------------------------|---------------------------------------------------------|---------------------------------------------------|------------------------------------------------------|-----------------|------------|
| 4      | 3                            | 67                                                      | 11                                                |                                                      | 4               | 100        |
| 5      | 6                            | 133                                                     | 22                                                |                                                      | 4               | 100        |
| 6      | 12                           | 267                                                     | 44                                                |                                                      | 4               | 100        |
| 7      | 24                           | 533                                                     | 88                                                |                                                      | 4               | 100        |
| 8      | 32                           | 1067                                                    | 176                                               | 1/3                                                  | 4               | 100        |
| 9      | 48                           | 1578                                                    | 264                                               | 1/2                                                  | 4               | 50         |
| 10     | 95                           | 2111                                                    | 352                                               | 1                                                    | 4               | 33         |
| 11     | 144                          | 3200                                                    | 528                                               | 1,5                                                  | 4               | 50         |

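### The 3 mg floor on the OIT start dose exceeds the reacting dose for children who react at the two lowest baseline challenge steps: ten-fold at 0.3 mg, marginally at 2.5 mg

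*Protocol*

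**What the plan says.** Protocol, Group 1, Visit 3 (start of immunotherapy) gives the rule: "The peanut OIT starts with 1/4 of the dose (at least 3 mg of peanut protein) that gave the first reaction at baseline challenge". Its worked example takes a reaction at 25 mg of peanut protein to a start dose of 6 mg. The day-1 procedure follows: "Four doses will be given at the study center with 20-30 min intervals with 0.8, 1.5, 3 and 6 mg of peanut protein". There is then 90 minutes of observation, and home dosing is conditional: "If the last dose of peanut protein is tolerated (in the example 6 mg), this dose will be ingested daily at home for 4 weeks".

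Eligibility limits the reacting dose from above only. The Inclusion criteria require "Positive baseline challenge at a maximum of the 250 mg peanut protein-dose", and the text on the baseline challenge randomizes after "objective symptoms at maximum dose 4 (250 mg peanut protein) and signed parental consent, the child will be randomized 2:1". The Exclusion criteria bar earlier life-threatening anaphylaxis, but not a low reacting dose.

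Table 2a sets the baseline steps at 0.3, 2.5, 25 and 250 mg. Table 3a gives the day-1 series, and its title limits it to low doses. The title of Table 3b states: "Starting dose is calculated from reaction dose at the baseline challenge". The first row of Table 3b is 3 mg, numbered dose 4.

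**The concern.** A quarter of the reacting dose is meant to start the child well below the amount that caused an objective reaction. The minimum of 3 mg works against this where sensitivity is greatest. It lies above both of the two lowest challenge steps, and nothing in the protocol keeps children who react at those steps out of the OIT arm.

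Followed as written, a child aged 12-47 months who reacted at 0.3 or 2.5 mg is given more than that dose on day 1 and, if it is tolerated, takes 3 mg daily at home. No separate rule covers these children. Nor does the Visit 3 section say what to do if the last day-1 dose is not tolerated; Table 4 is titled for symptoms outside the study center.

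**Working it through.** **Inputs.** Rule: a quarter of the reacting dose, minimum 3 mg (Group 1, Visit 3). Steps: 0.3, 2.5, 25, 250 mg (Table 2a). Day-1 series: 0.8, 1.5, 3, 6 mg (Visit 3, Table 3a). Schedule: Table 3b.

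**The protocol's own example.** 25/4 = 6.25 mg, which matches the stated 6 mg as the nearest Table 3b row.

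**All four steps.** Start dose = max(3, reacting dose/4); ratio = start dose / reacting dose.

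| Reacting dose (mg) | Quarter (mg) | Start by rule (mg) | Ratio |
|---|---|---|---|
| 0.3 | 0.075 | 3 | 10 |
| 2.5 | 0.625 | 3 | 1.2 |
| 25 | 6.25 | 6.25 | 0.25 |
| 250 | 62.5 | 62.5 | 0.25 |

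A child who reacts at 2.5 mg has taken 0.3 + 2.5 = 2.8 mg in total; 3/2.8 = 1.07.

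**Where the floor acts.** It replaces the quarter rule below 4 × 3 = 12 mg and exceeds the reacting dose below 3 mg. In Table 2a both ranges hold the same two steps, 0.3 and 2.5 mg.

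**Day-1 series.**
- 0.3 mg reactor: the first dose is 0.8/0.3 = 2.7 times the reacting dose. The amount given up to and including 3 mg is 0.8 + 1.5 + 3 = 5.3 mg, and 5.3/0.3 = 17.7.
- 2.5 mg reactor: the first two doses together are 0.8 + 1.5 = 2.3 mg, still below the reacting dose. Including the 3 mg dose the total is 5.3 mg, and 5.3/2.8 = 1.9 against the cumulative reacting amount.

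**The other reading of the bracket.** Grammatically, the minimum could qualify the dose that gave the reaction. The rule would then not cover a reaction below 3 mg, and those children would have no start dose. Because Table 3b begins at 3 mg, a floor on the start dose is the likelier meaning. Either way the rule needs correcting for the same children.

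**The case against.** The strongest reply is that the floor is written deliberately and that several safeguards surround it. Day 1 is a supervised titration in roughly two-fold steps, followed by 90 minutes of observation. The dose goes home only if it was tolerated, and families receive an adrenaline autoinjector. For the 2.5 mg reactor the first two doses stay below the reacting dose and the final excess is marginal. The protocol gives no frequency for such low reactions, and there may be none.

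Most of this stands, and it rules out some stronger readings that a reader might infer:

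- *That children are sent home on an untested ten-fold dose.* They are not; tolerance in the clinic comes first.
- *That the two groups are equally exposed.* The serious case is the 0.3 mg reactor.
- *That every child must go up to 6 mg on day 1, which would be 20 times 0.3 mg and 2.4 times 2.5 mg.* That sentence follows the 25 mg example. It cannot be universal, since a 250 mg reactor's start dose (62.5 mg by the quarter rule) lies far above 6 mg.
- *That nothing below 3 mg could serve as a step-back dose.* The visit text cites Table 3 as a whole. Table 3b starts at dose number 4 with a 100% increase, which presupposes a 1.5 mg step before it. The text is unclear, not prohibitive.

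The safeguards do not answer one thing: for a 0.3 mg reactor the first supervised dose already exceeds the dose that caused the reaction.

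**Conclusion.** The point holds and should be fixed on safety grounds. For eligible children reacting at the two lowest Table 2a steps, the rule sets a start dose above the reacting dose. The excess is large at 0.3 mg (10 times) and small at 2.5 mg (1.2 times, or 1.07 times the cumulative dose), where mainly the four-fold margin is lost.

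This assumes that the bracket is a floor on the start dose; otherwise these children have no defined start dose. The ratios apply per child. The documents do not support any estimate of how many children are affected or of how many reactions would follow.

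**What to change.** 1. State that the start dose is about a quarter of the reacting dose and never above it, and that the 3 mg floor does not apply to children reacting at 2.5 mg or less.
2. State that 0.8 and 1.5 mg, already in Table 3a, may be used as daily home and step-back doses, and that the day-1 series ends at the child's own start dose. A 2.5 mg reactor then starts at 0.8 mg (0.8/2.5 = 0.32 of the reacting dose). The 25 mg example is unchanged.
3. For 0.3 mg reactors, either start below 0.3 mg with one further ten-fold flour dilution, or do not start OIT. The investigators and the safety board should choose the option and the dose values. Weighing looks feasible: 0.1 mg, as an illustration, would be 0.1/0.046 = 2.2 mg of the 4.6% mix, or 22 mg after the further dilution, and Table 3a already weighs 17 mg.
4. State that if the last day-1 dose is not tolerated the child goes down one step, and that if the lowest step is not tolerated home dosing does not start.

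**Cost.** Protocol wording, two Table 3a doses carried into the home schedule, and possibly one dilution; no extra patients. The downside is longer up-dosing. From 3 mg there are 10 increases to 285 mg (40 weeks at 4-week steps, 60 at 6-week steps). From 0.8 mg there are 12 (12 × 4 = 48 weeks, 12 × 6 = 72 weeks), and from below 0.3 mg more still. Up-dosing ends at 60 weeks at whatever dose has been reached, so a few children may stop below 285 mg. At 6-week steps a child starting at 0.8 mg would have made 10 increases by week 60 and would be on 190 mg.
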